## Sample size {14}

The sample size of 200 per arm has been calculated assuming an odds ratio (*OR*) of 2, 85% power and a 2-tailed test at level *α* = 0.05 and allowing for approximately 10% of participants to be lost to follow-up. The odds ratio represents the odds of improvement in the ordinal scale for treatment relative to control.

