## Data collection and management

### Plans for assessment and collection of outcomes {18a}

Participant data will be collected using case reporting forms (on mobile tablets with REDCap®) to be completed by trained clinical research assistants at baseline all through day 15 and then day 29. The use of REDCap® with periodic data reviews by a data management and auditing team will help the research team maintain data quality.

The schedule of assessments is shown in Table 4 and illustrated in Fig. 1. See Supplements for case reporting forms.

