### Plans to promote participant retention and complete follow-up {18b}

Research participants in the treatment and control arms will be encouraged by the research team and given access to COVID-19 educational resources during the study. In addition, participants will receive communication from the research welfare team to attend to any concerns or questions participants may have during the study.

For participants who deviate or discontinue from the protocol, all outcome data relevant to the study prior to deviation or discontinuation from the study protocol will be collected.

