#### Statistical methods for analyzing the primary outcome

The primary hypothesis is that the clinical status measured by a 7-point ordinal scale for each of the investigational arms (1, 2, 3) will be different from that of the placebo arm.

Boschloo’s test will be used to evaluate this primary hypothesis in all randomized participants (intention-to-treat analysis). For each comparison of a given arm to control, only participants concurrently randomized to those two arms will be included. Statistical significance will be claimed if the two-sided *P*-value is less than the monitoring boundary allocating a total type I error rate of 0.05 across interim analyses. The Boschloo’s test is being used instead of Fisher’s exact test because the interim results, as well as results within subgroups, will have small sample sizes based on the multiple primary outcomes within the subgroups.

The ordinal scale will be used to estimate a proportional odds model. The primary hypothesis test will be based on a test of whether the common odds ratio for treatment is equal to one. Nonetheless, estimation and confidence intervals do require the model to be correct. Accordingly, we will evaluate model fit using a goodness-of-fit likelihood ratio test. A stratified hypothesis test to account for baseline severity of disease will be used.

The distribution of severity results will be summarized by treatment arm as percentages, and participants without final outcome data will be excluded from the analysis.

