### Methods in analysis to handle protocol non-adherence and any statistical methods to handle missing data {20c}

The analysis population will be based on intention-to-treat. No account will be taken for protocol non-adherence.

For missing data, patterns of missing data will be explored in the primary and secondary outcomes and reported. If required, multiple imputation statistical technique will be used assuming the mechanism of missing data is missing at random (MAR).

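### The primary analysis is called intention-to-treat, but its rules for missing day-15 scores conflict and allow a complete-case analysis chosen after the missing data have been seen

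*Protocol article*

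**What the plan says.** All references are to the protocol article.

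- **Statistical methods for analyzing the primary outcome.** The primary test is to be run "in all randomized participants (intention-to-treat analysis"). The section closes with a sentence on summarizing severity as percentages by arm, which ends "participants without final outcome data will be excluded from the analysis". No condition is attached to that exclusion.
- **Section {20c}, non-adherence and missing data.** "The analysis population will be based on intention-to-treat", and non-adherence is disregarded. Missing-data patterns in the primary and secondary outcomes are to be explored and reported. Then: "If required, multiple imputation statistical technique will be used assuming the mechanism of missing data is missing at random (MAR").
- **Section {18b}, retention and follow-up.** For participants who deviate or discontinue, "all outcome data relevant to the study prior to deviation or discontinuation from the study protocol will be collected".
- **Section {18a}, collection of outcomes.** Case report forms are completed "at baseline all through day 15 and then day 29".
- **Sample size {14}.** The target of 200 per arm was set "allowing for approximately 10% of participants to be lost to follow-up".

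**The concern.** An intention-to-treat comparison needs an outcome, observed or imputed, for everyone randomized. The primary-outcome section promises that and then removes those with no final score. Section {20c} offers a different rule, imputation, but does not say whether it replaces the exclusion. Because patterns are explored first, the choice can follow sight of the data.

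Section {18b} adds to the problem. It is the only rule specific to participants who deviate or discontinue, and it promises nothing after that point. A day-15 score could then be missing because the trial did not ask for it. Data not collected cannot be recovered later, and an assumption of missing at random is hard to support when nothing is observed after the participant leaves the protocol.

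At stake is the primary endpoint of a trial meant to inform a state, and possibly a national, treatment guideline.

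**Working it through.** **1. The plan's own figure.** Inputs from Sample size {14}: odds ratio 2, 85% power, two-sided alpha 0.05, about 10% loss, 200 per arm. The proportional-odds formula for n per arm is 6(z₀.₉₇₅ + z₀.₈₅)² / [(ln 2)² (1 − Σp̄³)], where p̄ is the mean category proportion over the two arms.

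- Numerator over (ln 2)²: 6 × (1.960 + 1.036)² / 0.4805 = 112.1.
- The control distribution is not given, so it is assumed. Distribution D is 65/15/10/5/2/1/2% over categories 1 to 7. It gives 1 − Σp̄³ = 0.626, so n = 112.1 / 0.626 = 179.2, and 179.2 / 0.9 = 199.1, rounded up to 200.
- Other assumed distributions give 128 (equal categories) to 314 (80% in the best category).

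The figure of 200 is therefore attainable but cannot be uniquely reproduced, and it is not shown to be wrong. At 10% loss, 200 × 0.10 = 20 participants per arm would be excluded.

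**2. Bias from exclusion when the drug has no effect.** Assumptions: 200 randomized per arm; control distribution D, or B = 42/16/20/12/4/3/3%; drop-out in categories 3 to 7 (hospitalized or dead) is m times that in categories 1 and 2 (not hospitalized).

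Worked case: D, 10% loss on active, 0% on control, m = 3.
- Base drop-out rate = 0.10 / (0.80 + 3 × 0.20) = 0.0714; in categories 3 to 7 it is 3 × 0.0714 = 0.214.
- Observed share not hospitalized on active = 0.80 × (1 − 0.0714) / 0.90 = 0.825, against 0.80 on control.
- Fitting the proportional-odds model to the expected counts gives a common odds ratio of 1.11 (log 0.108).
- Information = 180 × 200 / (3 × 380) × 0.708 = 22.4, so the standard error = 1/√22.4 = 0.211.
- Expected z = 0.108 / 0.211 = 0.51. Probability of a significant benefit = 1 − Φ(1.96 − 0.51) = 0.073.

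All cases (ranges cover B and D; false benefit is nominally 2.5%):

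| Loss, active vs control | m | Common odds ratio | False benefit |
|---|---|---|---|
| 10% vs 10% | 1 to 5 | 1.00 | 2.5% |
| 10% vs 0% | 2 | 1.06 | 5% |
| 10% vs 0% | 3 | 1.10–1.11 | 7–8% |
| 10% vs 0% | 5 | 1.14–1.18 | 11–12% |
| 15% vs 5% | 2 | 1.07 | 5–6% |
| 15% vs 5% | 3 | 1.12–1.13 | 8% |
| 15% vs 5% | 5 | 1.16–1.22 | 12–14% |

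Unequal loss with m = 1, unrelated to outcome, also gives 1.00 and 2.5%.

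**3. The opposite direction.** Take 30% not discharged in both arms (assumed) and a 10% loss on active only, all among the discharged. The observed not-discharged rate on active is 0.30 / 0.90 = 0.333. The odds ratio for discharge is (0.667 / 0.333) / (0.70 / 0.30) = 0.86, against the drug.

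**4. Complete follow-up.** If all randomized participants are scored, the null odds ratio is 1.00 and false benefit 2.5%, whatever the pattern of treatment discontinuation. Under D, power at odds ratio 2 is 0.89 with 200 scored per arm and 0.85 with 180.

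**The case against.** **The exclusion clause may be only a denominator.** It ends a sentence about percentages, so it could be confined to that summary. But it refers to the analysis, stands under the primary-outcome heading and is the only missing-data rule there. At best it is ambiguous.

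**Section {18b} does not say that collection stops.** This stands. It promises earlier data and is silent on later data, while {18a} and the Schedule of Assessments run to days 15 and 29. The gap is one of commitment, not a stated end of follow-up.

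**Drug toxicity as the route to missing scores.** A reader might infer that a participant taken off study drug under the liver or renal rules in section {11b} would lose the day-15 score and be excluded. The document does not support this. Those rules stop the drug, not participation. Scheduled safety bloods fall on days 1, 8 and 15, whereas chloroquine and hydroxychloroquine end on day 7, so no scheduled post-baseline test can stop either of them. Blinding also limits arm-related drop-out.

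**Who would be missing.** Hospitalized patients are assessed daily and a known death scores 7, so these are the best-observed participants. Missing scores are more plausible among the discharged, where the bias runs against the drug. This stands, and it is why no single direction can be claimed.

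**Some detail belongs in the statistical analysis plan.** The imputation model and the form of sensitivity analysis can wait for that document. Two rules that conflict within this one cannot.

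**Conclusion.** The point holds as a conflict between stated rules plus a gap in follow-up commitment. Followed as written, the primary analysis can be a complete-case analysis under an intention-to-treat label, with avoidable missing day-15 scores and a choice of method open until the missing data have been seen.

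The possible bias is moderate and conditional: a null odds ratio of about 1.06 to 1.22 and false benefit of about 5 to 14% under the unequal, outcome-related losses tabulated; none under equal loss by the same mechanism; and a reversed sign if the discharged are the ones lost. Only the 10% loss, odds ratio 2, 85% power, alpha 0.05 and 200 per arm come from the document. The category distributions, the split of loss between arms and the drop-out ratios are assumptions, and the rates use a normal approximation at z = 1.96 without the planned stratification or interim boundaries.

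A reader might go further and put the whole 10% loss among hospitalized or dead patients on the active arm. With 30% not discharged, that gives (0.30 − 0.10) / 0.90 = 0.222 and an odds ratio of (0.778 / 0.222) / (0.70 / 0.30) = 1.50. The document does not support that scenario: the 10% is a general allowance, not loss confined to one arm, and these are the patients under daily assessment.

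**What to change.** 1. In section {18b}, state that ordinal and vital status at days 15 and 29 are collected for every randomized participant regardless of deviation, treatment discontinuation or discharge, by telephone where needed, unless consent to follow-up is withdrawn.
2. In the primary-outcome section, delete the exclusion clause, or limit it explicitly to the descriptive percentages and a complete-case sensitivity analysis.
3. Reconcile that section with {20c}: make imputation on all randomized participants the single primary approach, replacing the conditional wording, and add a sensitivity check under a not-at-random assumption.

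The cost is revised protocol wording, some telephone calls and one extra analysis. No treatment rule changes.

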#### Statistical methods for analyzing secondary outcomes

The following analyses will be performed for the comparison of each experimental arm to the placebo arm when full enrolment has been achieved. For these analyses, the alpha level used is that of the analysis for the primary outcome when full enrolment has been achieved.
The Mantel-Haenszel odds ratio estimator and test statistic will be applied to the strata defined by clinical signs and symptoms (asymptomatic versus symptomatic).Differences in time-to-event endpoints (e.g. time to negative SARS-CoV-2 status) by treatment will be summarized with Kaplan-Meier curves and 95% confidence bounds.Change in ordinal scale at specific time points will be summarized by proportions (e.g. proportion who have a 1-, 2-, 3- or 4-point improvement or worsening).Duration of event (e.g. duration of mechanical ventilation) will be summarized according to median days with quartiles.Incidence data (e.g. incidence of new oxygen use) will be summarized as a percent with 95% confidence intervals.Categorical data (e.g. 28-day mortality or ordinal scale by day) will be summarized according to proportions with confidence intervals on the difference or odds ratios for a binary or multiple category scale, respectively.Logistic regression analyses will be undertaken to assess the effect of covariates on outcomes.

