## Introduction

### Background and rationale {6a}

#### Study rationale

The severe acute respiratory syndrome coronavirus 2 (SARS-CoV-2) causes the coronavirus disease 2019 (COVID-19), and it was first detected in Wuhan, China, in December 2019 [1]. COVID-19 disease was recognized as a pandemic by the World Health Organization (WHO) less than 3 months after on the 11th of March 2020 [2]. By July 1, 2020, more than 10,357,662 cases of COVID-19 had been reported, with about 508,055 deaths globally [3, 4]. COVID-19 outbreak forecasts and mathematical models suggest that the size of the population affected will continue to rise [5] in the coming months.

The virus is typically spread from one person to another via respiratory droplets produced during speech, coughing and sneezing [6]. Primarily, it spreads when people are in close contact, but it may also spread when one touches a contaminated surface and then their eyes, nose or mouth. It is most contagious when people are symptomatic, although spread may be possible before symptoms appear. The time between exposure and symptom onset is typically around 5 days but may range from 2 to 14 days. Fever and chills and dry cough, as well as shortness of breath, are commonly reported symptoms [1]. Complications may include pneumonia and acute respiratory distress syndrome. A WHO investigative report indicates that age over 60 years, diabetes mellitus, cardiovascular disease, chronic respiratory disease and cancer are associated with the highest risk of severe disease and death [1].

In Nigeria, a total of 26,484 cases and 603 deaths had been reported as of 1 July 2020 with Lagos alone accounting for about half of the cases [7]. The high proportion of cases contributed by Lagos State is likely due to the fact that it is the commercial capital with a large number of international travellers and has COVID-19 testing facilities and a very large population compared to other states.

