## Outcomes {12}

COVID-19 is a new disease and our understanding of it is evolving. To align this study with other international studies, the objectives, endpoints and some other aspects of the WHO’s Master Protocol [42] have been adopted as appropriate with modifications to suite the Lagos context. There are three objectives—one primary and two secondary objectives. Each objective has three sub-objectives—one for comparing chloroquine phosphate added on to standard therapy and standard therapy alone; one for comparing hydroxychloroquine sulphate added on to standard therapy and standard therapy alone; and one for comparing lopinavir/ritonavir added on to standard therapy and standard therapy alone.

A special WHO committee developed the ordinal scale that will be used in this study for the primary endpoint [43]. This study uses a combined endpoint (based on the WHO 7-point ordinal scale) of both “clinical status and mortality” at day 15. Hence, superiority can be demonstrated when either arm shows a significant effect on the variables for clinical status OR mortality by day 15. This endpoint is particularly useful in our population given the low mortality rate, and a combined endpoint would increase the study power. The secondary endpoints will enable evaluation of the effect of the trial medications on the rate of change in the clinical condition of COVID-19 patients, as well as the safety of the trial medications (Table 3).

**Table 3 Tab3:** LACTT objectives and endpoints

**Primary objectives**	**Primary endpoints**

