1. To evaluate the clinical efficacy of chloroquine phosphate, hydroxychloroquine sulphate and lopinavir/ritonavir added on to standard therapy relative to standard therapy alone for treatment of individuals with laboratory-confirmed COVID-19 1.1 To evaluate the clinical efficacy of chloroquine phosphate added on to standard therapy relative to standard therapy alone for treatment of individuals with laboratory-confirmed COVID-19 1.2 To evaluate the clinical efficacy of hydroxychloroquine sulphate added on to standard therapy relative to standard therapy alone for treatment of individuals with laboratory-confirmed COVID-19 1.3 To evaluate the clinical efficacy of lopinavir/ritonavir added on to standard therapy relative to standard therapy alone for treatment of individuals with laboratory-confirmed COVID-19	*Seven-point ordinal scale assessed on day 15* 1. Not hospitalized, no limitations on activities 2. Not hospitalized, limitation on activities 3. Hospitalized, not requiring supplemental oxygen 4. Hospitalized, requiring supplemental oxygen 5. Hospitalized, on non-invasive ventilation or high flow oxygen devices 6. Hospitalized, on invasive mechanical ventilation 7. Death
**Secondary objectives**	**Secondary endpoints**
1. To evaluate the effect of chloroquine phosphate, hydroxychloroquine sulphate and lopinavir/ritonavir added on to standard therapy compared to standard therapy on the rate of progression/resolution of COVID-19 1.1 To evaluate the effect of chloroquine phosphate added on to standard therapy compared to standard therapy on the rate of progression/resolution of COVID-19 1.2 To evaluate the effect of hydroxychloroquine sulphate added on to standard therapy compared to standard therapy on the rate of progression/resolution of COVID-19 1.3 To evaluate the effect of lopinavir/ritonavir added on to standard therapy compared to standard therapy on the rate of progression/resolution of COVID-19	1. Clinical status on the 7-point ordinal scale on days 3, 5, 8, 11 and 29 2. National Early Warning Score assessed daily while hospitalized and on day 15 3. Duration of supplemental oxygen 4. Duration of mechanical ventilation 5. Duration of hospitalization or isolation 6. SARS-CoV-2 clearance time based on samples taken on days 3, 5, 8, 11, 15 and 29

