#### Comparing time to meeting criteria for successful discharge from the COVID-19 treatment centre between participants receiving investigational therapeutics, relative to the control arm

Differences in median days to becoming eligible for discharge will be tested using the Wilcoxon rank-sum test, imputing deaths prior to day 28 as the worst rank, with earlier deaths having a worse rank than later deaths.Discharge decisions may not always be based on objective clinical data. For these reasons, time to meeting criteria for successful discharge will be analysed rather than time to actual discharge.We will tabulate the sample size, number (%) who became eligible for discharge within 29 days, mean, median and standard deviation of days to discharge eligibility among those for whom the endpoint is available. *P*-values for test of medians using Wilcoxon rank-sum test.Side-by-side plots and boxplots of time to meeting criteria for successful discharge by arm, separately for symptomatic and asymptomatic cases, will be prepared.

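### Time to SARS-CoV-2 clearance is summarized by Kaplan-Meier curves with no rule for deaths before clearance; cumulative incidence would be the better summary

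*Protocol article*

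**What the plan says.** In the protocol article, Table 3 under Outcomes {12} lists among the secondary endpoints "SARS-CoV-2 clearance time based on samples taken on days 3, 5, 8, 11, 15 and 29". The section on statistical methods for secondary outcomes names the method for time-to-event endpoints and uses this one as its example: "e.g. time to negative SARS-CoV-2 status) by treatment will be summarized with Kaplan-Meier curves and 95% confidence bounds". That section introduces its analyses as comparisons of each experimental arm with placebo. It says nothing about a participant who dies while still positive: not that death is censored, not that the participant stays at risk to day 29, and not that death is a competing event.

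For another favourable time outcome, time to meeting discharge criteria, the article does give a rule, in a Wilcoxon rank-sum test: "imputing deaths prior to day 28 as the worst rank, with earlier deaths having a worse rank than later deaths". The missing-data section {20c} mentions multiple imputation under missing at random, which is not a rule for deaths.

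On mortality, Outcomes {12} gives no rate for the trial population but explains the choice of primary endpoint thus: "This endpoint is particularly useful in our population given the low mortality rate". The study rationale reports for Nigeria that "a total of 26,484 cases and 603 deaths had been reported as of 1 July 2020".

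**The concern.** A participant who dies uncleared can never become negative, so death competes with clearance. If such a participant is censored at death, which is what Kaplan-Meier software users ordinarily do, the method treats the participant as someone who would have gone on to clear at the same rate as those still under observation. One minus the curve is then not the proportion of randomized participants who cleared. It exceeds that proportion by an amount that grows with the share dying uncleared.

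Because the curves are drawn to compare arms, the contrast is affected when mortality differs. An arm with more deaths has the larger overstatement, so the curves lean towards that arm, and the 95% bounds surround a quantity other than the share cleared. The trial enrols severe as well as mild and asymptomatic cases and has death as the worst category of its primary scale, so deaths before clearance are foreseeable.

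**Working it through.** The article states no figure for this endpoint, so there is nothing to reproduce. The check compares two summaries of the same process: one minus Kaplan-Meier with deaths censored, and the cumulative incidence of clearance with death as a competing event.

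**Inputs from the document**
- Sampling on days 3, 5, 8, 11, 15 and 29 (Table 3).
- National crude mortality 603/26,484 = 0.0228, about 2.3% (study rationale). Using it here assumes that it applies to the trial and that every death occurs before clearance.

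**Inputs assumed**
- Clearance hazards equal between arms, at the values given below.
- Other shares dying uncleared: 4.6% (double 2.3%), 8% and 10%.

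**Model 1: constant hazards, median clearance 10 days, 28 days of follow-up**
- Clearance hazard: l = ln 2 / 10 = 0.0693 per day.
- One minus Kaplan-Meier: 1 − exp(−28 l) = 0.856. The death hazard m does not enter.
- Cumulative incidence of clearance: l/(l+m) × [1 − exp(−28(l+m))], with m solved so that m/(l+m) × [1 − exp(−28(l+m))] equals the share dying uncleared.

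| Dying uncleared | m per day | 1 − KM | Cumulative incidence | Overstatement |
|---|---|---|---|---|
| 2.3% | 0.0019 | 85.6% | 84.1% | 1.5–1.6 points |
| 8% | 0.0069 | 85.6% | 80.2% | 5.5 points |
| 10% | 0.0088 | 85.6% | 78.8% | 6.9 points |

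Check of the first row: l + m = 0.0712; exp(−28 × 0.0712) = 0.136; (0.0693/0.0712) × 0.864 = 0.841.

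With 8% in one arm and 2.3% in the other, the cumulative incidences differ by 84.1 − 80.2 = 3.9 points. The Kaplan-Meier values are identical, because the clearance hazard was set equal.

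**Model 2: constant hazards to day 29, with 1 − KM varied from 70% to 95%.** The overstatement is 1.1 to 1.9 points at 2.3% dying uncleared, 2.3 to 3.9 points at 4.6%, and 4.9 to 8.5 points at 10%.

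**Model 3: the article's own visits**, with assumed clearance probabilities of 0.10, 0.12, 0.25, 0.30, 0.40 and 0.50 at successive visits among those alive and uncleared.
- 1 − KM = 1 − (0.90 × 0.88 × 0.75 × 0.70 × 0.60 × 0.50) = 87.5% at every death rate.
- Cumulative incidence is 87.5%, 85.7%, 83.8% and 79.4% for 0%, 2.3%, 4.6% and 10% dying uncleared.
- The gap at 2.3% is 87.5 − 85.7 = 1.8 points, in line with the other models.

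**The alternative coding.** If uncleared deaths are kept in the risk set as not cleared to day 29, and nobody else is censored, one minus Kaplan-Meier equals the cumulative incidence. The problem then disappears.

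**The case against.** The strongest reply is that the article nowhere says deaths are censored. A Kaplan-Meier curve that holds uncleared deaths at risk to day 29 would satisfy the same sentence, and the coding of deaths may be settled in the analysis plan, which is not shown. That stands as far as it goes: censoring at death is the usual convention, not a written rule. But the method is fixed in the article, its ordinary application gives the wrong quantity here, and a better one is available from data already collected. The point is therefore more than a missing detail.

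Three stronger readings are tempting, and the document does not support them.
- A reader might infer that the plan treats death in two incompatible ways. It does not: there is a rule for discharge eligibility and silence for clearance, and silence contradicts nothing.
- A reader might infer that clearance time carries all the virological evidence. It is the only virological item in Table 3, but viral status at days 15 and 29 is also compared with control by Boschloo's test, in the section headed as a comparison of mortality rates.
- A reader might infer that the written plan would show a harmful drug with no loss of clearance. That is exact only if deaths are censored and the clearance hazards are equal.

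A harmful drug would not go unseen either. An 8% against 2.3% contrast is 0.057 × 200 = 11.4 extra deaths per 200 participants. Deaths enter category 7 of the primary scale, and 28-day mortality is summarized by arm. Serious adverse events are compared with control and reviewed at three interim looks.

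The error is also small beside sampling noise. With 200 per arm and 85.6% cleared, the 95% half-width is 1.96 × √(0.856 × 0.144/200) = 4.9 points for one arm and √2 times that, 6.9 points, for a difference. This limits the importance of the point. A systematic lean in a known direction is still worth removing when doing so is cheap.

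**Conclusion.** The concern holds in a limited form. The article names Kaplan-Meier for time to clearance without saying how deaths before clearance are handled. Under the usual convention, the resulting figure overstates the share cleared and is insensitive to mortality differences between arms.

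At 2.3% dying uncleared, the overstatement is about 1 to 2 points per arm, and it largely cancels if mortality is equal. It reaches about 4 points between arms only under an assumed 8% against 2.3%; the 8% appears nowhere in the document, which expects low mortality. The sizes rest on censoring at death, equal clearance hazards between arms, the assumed clearance rates, and the national crude figure standing in for deaths before clearance in this trial. This is a worthwhile, inexpensive improvement to a secondary summary and does not touch the primary analysis.

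**What to change.** In the section on statistical methods for secondary outcomes, replace Kaplan-Meier for time to negative SARS-CoV-2 status with the cumulative incidence of clearance by arm, treating death before clearance as a competing event (Aalen-Johansen estimator, with 95% confidence bounds). Alternatively, keep the Kaplan-Meier wording and add that participants who die uncleared remain in the risk set as not cleared to day 29. This follows the spirit of the worst-rank rule for discharge eligibility. The two give the same result when there is no other censoring. Since the article allows for about 10% loss to follow-up, the Aalen-Johansen form is the cleaner choice.

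The cost is a sentence in the protocol or analysis plan and a small amount of extra analysis work with standard R functions. Deaths are already recorded through the primary scale, so no new data are needed.
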